### Clinical Trial Objectives

This study aimed to determine whether CPAP or PT initiated by the 16th week of gestation in pregnant women with a respiratory disturbance index (RDI) or AHI ≥5 results in improved clinical outcomes, particularly in relation to the development of gestational diabetes.

### Trial Feasibility Objectives

This study aims to assess the feasibility and acceptability of trial interventions and schedule of visits and determine limitations of trial design, including patient and hospital staff participation.

## Methods

All trial primary and secondary outcomes are described in the Australian New Zealand Clinical Trials Registry Trial Registry.

### Ethics Approval and Consent to Participate

#### Overview

Participant recruitment commenced on September 10, 2019. The final patient was recruited in December 2022 and is expected to complete participation in June 2024. The participants affected by product recalls in this trial will be followed up annually for 5 years, if agreeable as per the protocol. Data from participants who choose to withdraw from study participation will be included in the final analysis unless requested by the participant. The trial was registered on November 6, 2019 (ACTRN12619001530112), 7 weeks after the first participant was recruited for the study. The study protocol was not amended during this time.

#### Human Subject Ethics Review Approvals or Exemptions

The South Western Sydney Local Health District Human Research and Ethics Committee (SWSLHD HREC) approved this study (June 12, 2019, project identifier 2019/ETH00283). The current protocol version 3.1 was approved on November 11, 2022.

#### Informed Consent

The participants with scheduled antenatal bookings at Liverpool and Campbelltown hospitals will be invited to undertake a screening eligibility preconsent questionnaire, which is presented in Multimedia Appendix 1 by research study staff to determine participation eligibility as described in the eligibility criteria above. Women will be sequentially approached.

Following the screening, study staff will invite eligible participants to provide written informed consent. Multimedia Appendix 2 presents the postconsent baseline information questionnaire, which will be collected at the next trial consent.

The participants will undertake attended polysomnography to determine eligibility in the RCT. Additionally, the participants will be invited to undertake Apnealink Air and Somte at both the baseline and 28- to 32-week gestation periods, in addition to the attended polysomnography as part of a substudy assessing agreement in AHI or RDI scores in the early to mid-gestation period. Sleep studies will be undertaken within a 7-day window, where practicable. Completion of Apnealink and Somte are not required for RCT participation but will be used to determine the validity of these tests for future use in this population. Eligibility for participation in RCT will be determined by polysomnography outcome.

Women who undergo polysomnography by 14-week gestation period and demonstrate OSA as evidenced by an RDI or AHI ≥5 on polysomnography will be invited to participate in the RCT provided exclusion criteria are not met as described above. A second written informed consent will be collected by study staff, and the participants will be randomized to CPAP, PT, or control as described in the randomization section below.

Validation of home sleep testing in this population will be undertaken via a separate substudy. After validation of the home testing method, further recruitment and screening measurements will continue with screening questionnaires and home Apnealink Air only.

#### Privacy and Confidentiality

Unattended polysomnography, Apnealink Air, and biomarker data will be deidentified, as described in the relevant methods sections below. Patient data are deidentified for the purpose of randomization, as described below.

Participant consent forms, printed results, and other identifying information on hard copy will be stored in a locked cabinet in a security-access area of the Respiratory and Sleep Medicine Research Department at Liverpool or Campbelltown Hospitals. Where possible, study data will be stored separately to participant identifiers. A master list of study ID numbers and participant identifiers will be stored electronically in a password-protected file within a designated electronic folder on the Respiratory Research drive on the secure Liverpool Hospital server. A separate password-protected folder will be designated for any electronic records with results and identifying information.

#### Compensation

If the participants suffer any harm, they will be compensated as per health authority regulations.

### Trial Design

Pregnancy-associated obstructive sleep apnea (POSA) is a 2-center randomized controlled feasibility trial. The participants will be recruited following participation in an observational study by our group that assesses diagnostic validation of Apnealink air and Somte devices and long-term fetomaternal outcomes. The participants will also be approached at antenatal visits or called by telephone to assess eligibility. Recruitment at both study sites will be concurrent, and the participants who meet the eligibility criteria based on AHI or RDI results in the observational study will be approached for participation in the RCT.

The RCT will use a parallel group, individually randomized, open-label design with two interventions and one control group (1:1:1), with minimization allocation among the 3 arms stratified for BMI, previous history of preeclampsia, or gestational diabetes mellitus. A total of 48 participants (16 in each arm) will be recruited. Study visits will occur monthly after randomization until 32-week gestation period and fortnightly thereafter until delivery, as is local routine clinical practice for antenatal visits. Data collection will include demographic, clinical and physical details, sleep questionnaire responses, sleep study data, maternal pathology, fetal scans, birth details, maternal and fetal clinical outcomes, sleep therapy compliance, and therapy acceptance questionnaires.

We used the SPIRIT (Standard Protocol Items: Recommendations for Interventional Trials) checklist when writing our protocol [30], which can be found in Multimedia Appendix 3.

### Trial Setting

POSA will be conducted at Liverpool Hospital (LPH) and Campbelltown Hospital (CTN) public hospitals within the South Western Sydney Local Health District in metropolitan Sydney, New South Wales, Australia. LPH is a tertiary referral center offering comprehensive antenatal services, delivering approximately 4000 women annually, and includes a level 6 neonatal intensive care unit for neonates from a 24-week gestation period in the district and a comprehensive sleep and respiratory service, including a 5-bed sleep laboratory, ambulatory testing, and a comprehensive outpatient service, including clinics for CPAP therapy. CTN delivers approximately 4200 women annually, with a level 4 nursery that cares for neonates from a 32-week gestation period and a general respiratory and sleep clinic, without the capacity to undertake polysomnography. POSA participants recruited from CTN will be referred to LPH for laboratory polysomnography.

### Eligibility Criteria

Eligible participants are defined as women aged 18 years of age and older; in early pregnancy (up to 14-week gestation period); at increased risk of metabolic complications defined as one or more of (1) BMI greater than or equal to 35 kg/m^2^, (2) previous GDM, (3) previous personal history of preeclampsia (or in mother or sister), (4) underlying renal disease, (5) maternal type 2 diabetes (pregestational), and (6) symptoms of SDB including snoring, witnessed apnea, mild excessive daytime sleepiness (EDS; which does not meet the criteria for severe EDS defined by Epworth Sleepiness Scale (ESS>15), or a fall asleep accident, or near-miss accident in the previous 12 months), or tiredness; and obstructive sleep apnea diagnosed by polysomnography defined as RDI or AHI ≥ 5.

The participants will be excluded if they have (1) a previous diagnosis of OSA on active treatment, (2) confirmed GDM or preeclampsia, (3) maternal type 1 diabetes, (4) multifetal gestation, (5) known fetal chromosomal abnormality, (6) inability to provide informed consent, and (7) severe EDS based on clinical assessment (eg, including a fall asleep motor vehicle accident or near miss, transient sleepiness while driving or at lights or needing to pull over due to sleepiness while driving, or transient sleepiness in any other dangerous situation, ie, cooking, carrying a baby) or ESS of greater than 15.

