**Methods:**

This study is a randomized, controlled, open-label feasibility study in which pregnant women with an apnea-hypopnea index (AHI) or respiratory disturbance index (RDI) ≥5 are treated with CPAP (auto-titrating and fixed pressure) or positional therapy from early gestation (by 16 weeks) until delivery. The primary outcome is the feasibility of the study protocol and the development of gestational diabetes mellitus by the 28-week gestation period. Secondary outcomes include the development of hypertensive disorders of pregnancy (HDP), maternal weight gain, uterine artery blood flow, glycemic control during pregnancy (in participants who develop gestational diabetes), changes in maternal circulating biomarkers, and neonatal birthweight complications. Polysomnography at 28- to 32-week gestation period, postpartum polysomnography, therapy compliance, and patient acceptability are also assessed.

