### Randomization, Allocation, Concealment, and Blinding

The participants will be individually randomized via a telephone call to the National Health and Medical Research Council’s Clinical Trials Centre at Sydney University, who are independent of the trial, by the study coordinator. Randomization will be based on a minimization method with stratification for previous preeclampsia, personal history of gestational diabetes, and BMI≥35, to either CPAP, PT, or control groups. A maximum imbalance value of 1 between any of the 3 arms will be used in determining whether a forced allocation (ie, to achieve minimization of difference of stratification factor totals) or random allocation is used in a specific subject randomization. Treatment allocation will be unblinded for both study staff and participants.

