### Outcome Assessment

An oral glucose tolerance test will be undertaken for the assessment of gestational diabetes at 28 weeks (in addition to earlier testing if clinically requested). Collection of fasting blood will be followed by administration of 75 g oral glucose load, with 1 and 2 hours of blood collection. Interpretation will follow the Australasian Diabetes in Pregnancy Society (ADIPS) 2020 guidelines [38].

Blood pressure (BP) will be recorded at each study visit. Diagnosis of HDP will be defined as per the Society of Obstetric Medicine of Australia and New Zealand (SOMANZ) guidelines [39].

Anthropometric measurements (height, weight, and BMI) will be recorded during the randomization visit, and weight will be checked at subsequent study visits by study staff using hospital clinic scales.

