### Statistical Methods

This trial is a feasibility trial, and as such, no power calculations for the RCT were derived. We prespecified to assess the diagnostic accuracy of the home sleep tests as well as the screening questionnaires following the STARD (Standards for Reporting of Diagnostic Accuracy) guidelines. The accuracy will be assessed at various cutoff points using a receiver operating characteristic curve. The area under the receiver operating characteristic curve and positive and negative predictive values in the patient population will be derived. The first recruitment target will be 50 participants, which provides at least 80% power (α=.05) to detect a C-statistic of 0.7 when the allocation ratio is 1 (ie, 50% prevalence) and 0.75 when the allocation ratio is 2 (ie, 20% prevalence). We will be comparing Apnealink Air and SOMTE unattended PSG to attended PSG. Further exploratory analysis will be undertaken to assess whether any factors at booking, including the results of the sleep questionnaire, biomarkers, clinical factors, and history in combination with findings of unattended PSG, Apnealink, or attended PSG, are predictive of poor outcomes (either maternal or fetal, as discussed above). A composite of the combined adverse maternal outcomes and combined adverse fetal outcomes will also be assessed as an outcome. Data will be displayed as mean (SD), 95% CIs, and median (IQR) as appropriate based on data distribution. An intention-to-treat analysis will be undertaken for the primary outcome as well as the secondary outcomes. A per-protocol analysis (for primary and secondary outcomes) will also be undertaken, and both data will be presented. A *P* value of <.05 will be considered statistically significant. Where multiple analyses are undertaken, adjustments will be made for multiple comparisons. Longitudinal analysis of repeated measures will be undertaken where measurements are undertaken several times. Where differences at baseline exist between the groups, adjustments will be made statistically. Where less than 10% of any data point is missing, data will be imputed. We have preplanned an exploratory analysis of flow characteristics of all sleep tests to investigate sub-criterion flow changes related to long-term fetomaternal outcomes.

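### Women with pregestational type 2 diabetes are eligible but cannot develop gestational diabetes, and the intention-to-treat analysis of that primary outcome is not limited to women at risk

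*Protocol article*

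**What the plan says.** All references are to the Protocol article.

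- **Eligibility Criteria.** One of the qualifying metabolic risk criteria is "5) maternal type 2 diabetes (pregestational". The exclusions that concern diabetes are in "2) confirmed GDM or preeclampsia, (3) maternal type 1 diabetes". Type 2 diabetes is not excluded.
- **Abstract, Methods.** "The primary outcome is the feasibility of the study protocol and the development of gestational diabetes mellitus by the 28-week gestation period".
- **Clinical Trial Objectives.** The clinical aim is improved outcomes, "particularly in relation to the development of gestational diabetes".
- **Outcome Assessment.** "An oral glucose tolerance test will be undertaken for the assessment of gestational diabetes at 28 weeks". The section gives no separate rule for women already known to have diabetes.
- **Statistical Methods.** "An intention-to-treat analysis will be undertaken for the primary outcome as well as the secondary outcomes". Also: "A per-protocol analysis (for primary and secondary outcomes) will also be undertaken, and both data will be presented". Neither sentence limits the GDM comparison to women at risk of GDM.
- **Introduction, last paragraph.** The trial is to yield preliminary recruitment and efficacy data that may serve to design and power a larger trial.

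**The concern.** Three stated parts of the plan do not fit together. Eligibility admits women whose diabetes predates the pregnancy. The outcome is diabetes that develops during it. The analysis set keeps every woman in her assigned arm. By the article's own terms pregestational diabetes and newly developed GDM are different conditions, so a woman with the first is not at risk of the second.

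The per-protocol analysis does not remove her, because an eligible participant is not a protocol deviation on that account. The article does limit a glycaemic outcome elsewhere: in the Abstract, the secondary outcome of glycaemic control is confined to women who develop GDM. The primary outcome has no matching limit.

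At stake are the GDM rate per arm and the estimated effect. Both would depend partly on how many women not at risk happened to enter, and a later sample size could be built on them.

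**Working it through.** The article states no figure on this point to reproduce; it derives no power for the randomised comparison. The check therefore sizes the consequence.

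**Inputs**
- 16 women per arm, 48 in total (Trial Design; 3 × 16 = 48).
- Assumed: GDM risk among women at risk of 30% in control and 15% in a treated arm. The article gives neither.
- Assumed: k of the 16 women in an arm have type 2 diabetes, so f = k/16. The article does not give this share, so a range is shown.

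**1. Women with type 2 diabetes counted as non-events, equal shares in both arms**

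The observed rate is p(1 − f). The risk difference is (0.30 − 0.15)(1 − f). The relative risk is 0.15(1 − f) / [0.30(1 − f)] = 0.50 whatever f is.

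For a later two-arm comparison (two-sided 5%, 80% power), n per arm = [1.96√(2p̄(1 − p̄)) + 0.842√(p₁(1 − p₁) + p₂(1 − p₂))]² / (p₁ − p₂)². The last column is the number to recruit per arm if such women are still enrolled but only women at risk are analysed: 121/(1 − f), rounded up.

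| k of 16 | f | Control | Treated | Risk difference (points) | n per arm, counted as non-events | n per arm, at-risk analysis |
|---|---|---|---|---|---|---|
| 0 | 0 | 30.0% | 15.0% | 15.0 | 121 | 121 |
| 1 | 6.25% | 28.1% | 14.1% | 14.1 | 131 | 130 |
| 2 | 12.5% | 26.3% | 13.1% | 13.1 | 143 | 139 |
| 3 | 18.75% | 24.4% | 12.2% | 12.2 | 157 | 149 |
| 4 | 25% | 22.5% | 11.25% | 11.25 | 173 | 162 |

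Most of the rise above 121 comes from enrolling women who carry no information on GDM. Counting them as non-events adds a little more (143 against 139 at k = 2).

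**2. Unequal shares, no treatment effect, 30% risk**

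If one arm has two more such women than another, the rates differ by 0.30 × 2/16 = 0.0375, about 3.8 points, with no true effect. With two independent Binomial(16, f) counts, the chance that two given arms differ by two or more such women is 20%, 36% and 50% for f = 5%, 10% and 20%. This treats allocation as simple randomisation; the minimisation actually used could change it somewhat.

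**3. Scale of that shift**

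The standard error of one arm's rate is √(0.30 × 0.70/16) = 0.115. For a difference between two arms it is √2 × 0.115 = 0.162. A 3.75-point shift is 3.75/16.2 = 0.23 of that standard error.

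**4. If the 28-week glucose test were read as GDM in these women**

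Each rate becomes p(1 − f) + f. The risk difference is diluted exactly as in the table, and the relative risk moves from 0.50 to 0.59, 0.66 and 0.76 at k = 1, 2 and 4. The article does not show that this coding would be used.

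**The case against.** The strongest reply is that this is an article about an unpowered feasibility pilot. The denominator for a single outcome is often left to an analysis plan that is not shown here, and Statistical Methods does not say outright that every randomised woman enters the GDM denominator. Sampling error at 16 per arm also exceeds the distortion, as step 3 shows, and with equal shares and non-event coding the relative risk is untouched. All of that stands as a limit on size. It does not remove the point, which rests on what the article does state: who is admitted, what the primary outcome is, and an intention-to-treat analysis with no at-risk limit.

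A second reply is that if the larger trial keeps the same criteria, the rate among all entrants is the right planning figure, and that diabetes status is known at entry so the rate can be recalculated. This is true provided the share with type 2 diabetes and the coding are the same in both trials. Reporting that number per arm makes the recalculation possible.

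A third reply is that Statistical Methods promises adjustment for baseline differences. That addresses chance imbalance, but it neither defines who is at risk nor settles how the others are counted.

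Two stronger readings are tempting, and the documents support neither.

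- A reader might set the two codings side by side. With 3 of 16 women affected, an arm reads 24.4% as non-events or (0.30 × 13 + 3)/16 = 43.1% as GDM, a swing of about 19 points. The higher figure needs women with known prior diabetes to be counted as having developed GDM, which the article does not show and which sits badly with its outcome wording. The swing is also a contrast between two codings of one arm, not a difference between arms, since one rule would apply to all arms.
- A reader might fault the allocation because type 2 diabetes is absent from "stratification for previous preeclampsia, personal history of gestational diabetes, and BMI≥35". Three factors for 48 women is a reasonable choice, and leaving out a fourth is not an error.

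**Conclusion.** The point holds as a mismatch between eligibility, outcome and analysis set. Followed as written, the plan puts women who cannot have the event into the GDM comparison.

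The size is modest. With non-event coding and an assumed 30% risk, an arm reads 24.4% to 28.1% with three to one such women of 16. The risk difference shrinks by (1 − f), and an imbalance of two women shifts it by about 3.8 points. These figures rest on assumed GDM risks and an assumed share with type 2 diabetes; if few or no such women were randomised, the effect is small or nil.

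The damage is mainly to the preliminary GDM rates and effect estimates offered for planning. The feasibility part of the primary outcome and the other outcomes are not affected. This should be fixed before the analysis, but a pilot of 48 women with no power calculation cannot support a confirmatory GDM conclusion in any case, so it does not threaten the trial as a whole.

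**What to change.** Define the GDM analysis set as all randomised women without pregestational diabetes, analysed in the arm to which they were randomised. Keep women with type 2 diabetes in feasibility and in every other outcome. Report their number per arm beside the GDM result.

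Diabetes status is fixed before randomisation, so the restriction keeps the randomised comparison intact. Recruitment ended in December 2022 (Ethics Approval and Consent to Participate, Overview), so the change is to the analysis only and alters nothing for participants. It takes one sentence in the analysis plan, settled before the GDM results are compared by arm. The downside is a slightly smaller GDM denominator, for example 14 instead of 16 in an arm with two such women.

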### Interventions

All groups will have antenatal care as usual without restriction during the trial. The participants will be randomized to CPAP, PT, or control, and the participants randomized to intervention (CPAP or PT) will undertake therapy device education at the randomization visit and commence therapy on the day of randomization or as soon as is practicable. The participants will also be encouraged to use their therapy device for all sleep periods (including naps) from randomization until delivery. CPAP and PT devices will be returned following delivery or withdrawal or discontinuation from the study. The CPAP masks used by the study participants may be retained at the end of the study.

All participants will undertake polysomnography at the 28- to 32-week gestation period. CPAP or PT intervention participants will complete polysomnography at a 28- to 32-week gestation period with the device in situ to confirm treatment efficacy. CPAP will be titrated, if required, as described above. In addition, participants will be invited to complete Somte and Apnealink at 28- to 32-week gestation period, as part of the device validation substudies.

### CPAP Intervention

The participants in the CPAP intervention group will use a close-fitting facial mask worn overnight during sleep to ensure that the collapsible upper airway is kept patent with a column of air and they will commence on auto-titrating pressure 6-20 cm H_2_O (Philips Dreamstation Auto with heated humidification) per clinical practice at the study site. The participants will also be offered a range of CPAP masks to trial with an option to take home multiple masks or sizes if needed. CPAP participants will be educated in device use and troubleshooting by an experienced sleep therapist before commencing therapy. The trial sleep therapist will telephone CPAP group participants on day 3 to gain access to CPAP efficacy data via remote monitoring software (Care Orchestrator, Philips). Pressure will be changed to the 90th percentile pressure in fixed pressure mode, provided compliance data show average usage of CPAP across a period of more than 4 hours (All Days≥4 hours), and treatment efficacy is achieved as determined by residual AHI≤5. The participants with poor compliance or efficacy will be given additional acclimatization time on CPAP, up to 7 days (or as clinically necessary), and changed to the 90th percentile when clinically appropriate. CPAP data will be downloaded via Secure Digital card (SD) data card and reviewed at each study visit and at the return of the device as per the study schedule and interrogated for CPAP compliance, efficacy, and mask leak.

CPAP pressure will be adjusted empirically at scheduled study visits to maintain treatment efficacy (AHI≤5). Polysomnography will be conducted at 28 weeks on the current CPAP pressure. Titration of CPAP pressure will be undertaken if criteria for pressure increase is met per AASM (American Academy of Sleep Medicine) manual titration guidelines, that is, up to 1 increase by 1 cm H_2_O per 5-minute period for any of the following: 2 of obstructive apneas, 3 of hypopneas, 5 of the respiratory event–related arousals, or 3 minutes of loud or unambiguous snoring [31]. CPAP pressure changes will be reported in published study findings at the conclusion of the trial.

Compliance and efficacy of treatment feedback will be provided to study participants at each visit to encourage compliance. Additional phone or video support will be available, at participants’ request, for participants who encounter difficulty with CPAP compliance. To ensure equal therapy support for CPAP and PT treatment arms, remote monitoring of CPAP compliance will not be conducted beyond the acclimatization period. CPAP devices used in this trial have been replaced by the manufacturer in accordance with the Therapeutics Goods Administration device repair or replacement program following product defect correction order RC-2021-RN-01373-1.

